### Concomitant Medications

The concomitant administration of any other medication, including antipyretics and antiemetics, will be at the discretion of the physician to provide adequate care. However, it is recommended that no unnecessary concomitant medication be used. In particular, the use of antibiotics, diosmectite, probiotics, or racecadotril (all included in the exclusion criteria) should be avoided.

### Follow-Up

All study participants will be followed up for the duration of the intervention (5 days) and then for an additional 3 days or until the cessation of diarrhea.

### Outcomes

The primary outcome will be the duration of diarrhea, defined as the time until the normalization of stool consistency according to the BSF or ASF scale (in BSF scale, numbers 1, 2, 3, 4, and 5; in ASF scale, letters B or C) or the time until the normalization of the number of stools (compared with the period before the onset of diarrhea) and the presence of normal stools for 48 hours.

Secondary outcomes will include:

Need for intravenous rehydrationDuration of intravenous rehydrationNeed for hospitalization of outpatientsNumber of watery stools per dayVomitingRecurrence of diarrhea (48 hours after intervention)Severity of diarrhea according to Vesikari scale [22]Use of concomitant medicationsAdverse events

### Randomization

A computer-generated randomization list will be prepared by a person with no clinical involvement in the trial using a computer program (StatsDirect, StatsDirect Ltd.) with an allocation ratio of 1:1 and a block of 6. The randomization lists will be stratified according to rotavirus vaccination status (nonvaccinated and vaccinated; the latter will be defined as receiving at least 1 dose of rotavirus vaccine).

### Allocation Concealment

The allocation sequence will be concealed from the researchers enrolling and assessing participants in sequentially numbered, white, opaque, sealed and stapled envelopes which will be opened only after getting informed consent and registering the basic demographic data to case report form (CRF). Consecutive randomization numbers will be given to participants at enrollment. The study product will be packaged as product A or product B and will be given according to the randomization list.

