### Blinding

The study products (active and placebo) will be packaged in identical bottles. Contents will look and taste the same. Researchers, caregivers, outcome assessors, and a person responsible for the statistical analysis will be blinded to the intervention until the completion of the study. The information on intervention assignments will be stored in a sealed envelope in a safe place in the administrative part of the department. The personal information about potential and enrolled participants will be stored in a locker within the study site, accessible to the involved researchers only.

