### Power Calculation

The primary outcome of the study is the duration of diarrhea. Based on available data in the literature, the average duration of gastroenteritis in children is 5 to 7 days [3]. We assume that a clinically significant difference in the effectiveness of *L reuteri* DSM 17938 versus placebo will shorten the duration of symptoms by 24 hours (±24 hours). To detect such a difference in the duration of diarrhea between the study groups with a power of 90% and alpha of 0.01, a sample of 60 children is needed. Assuming approximately 20% loss to follow-up, we aim to recruit a total of 72 children for this study. A similar sample size for rotavirus vaccinated and nonvaccinated children is planned. Sample size calculations were performed with StatsDirect version 2.3.8 (StatsDirect Ltd).

At the Department of Paediatrics of St Hedwig of Silesia Hospital, there are 300 admissions of children with diarrhea per year and the same number of such patients who present to the emergency room. Assuming that 20% of these children will be eligible for the study, we will achieve adequate participant enrollment to reach the target sample size during 1 year of recruiting for rotavirus nonvaccinated children. Recruitment of rotavirus-vaccinated children may be slower (up to 2 years). In Poland, rotavirus vaccination has been recommended since 2006; however, vaccine reimbursement is not available. Hence, currently, the rotavirus vaccination coverage rate is low (12.7% [23] to 30% [24]), likely due to the high vaccine cost.

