## Results

The recruitment started in January 2017 and is planned to be finalized in June 2018 for rotavirus nonvaccinated children. The recruitment of rotavirus-vaccinated children may be slower due to a relatively low coverage rate in Poland. Data analysis and submission to a peer-reviewed journal is expected within 3 months after completion of the study.

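### A two-letter product code with one published block size of 6 makes the next letter partly predictable, and the plan does not say which study's completion lifts the blind

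*Protocol article*

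**What the plan says.** The Allocation Concealment section fixes the product code: "The study product will be packaged as product A or product B and will be given according to the randomization list". It adds "Consecutive randomization numbers will be given to participants at enrollment" and describes "sequentially numbered, white, opaque, sealed and stapled envelopes which will be opened only after getting informed consent".

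The Randomization section has the list generated "with an allocation ratio of 1:1 and a block of 6", and "The randomization lists will be stratified according to rotavirus vaccination status". It gives no second block size. The Ethics and Dissemination section says the protocol will be open access, so the block size is public.

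The Blinding section says: "Researchers, caregivers, outcome assessors, and a person responsible for the statistical analysis will be blinded to the intervention until the completion of the study". It describes one sealed envelope holding the assignment information, kept in the department's administrative area. The Abstract calls the vaccinated and nonvaccinated parts two separate studies, and the Statistical Analysis section plans a report for each. Under Results, recruitment is "planned to be finalized in June 2018 for rotavirus nonvaccinated children", with submission expected within 3 months of completion. The Power Calculation section allows up to 2 years for the vaccinated children.

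**The concern.** Opaque envelopes hide the next assignment. They do not hide earlier ones when every bottle carries one of two letters. Someone who knows the block length and keeps a tally can work out the last letter or letters of each block before deciding whether to approach the next family. That weakens the protection against selective enrolment.

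Blinding has a related weakness. With only two codes, learning what one child received, for example through a code break, shows what every child with the same code received. Duration of diarrhea rests on a caregiver diary of stool number and consistency. Physicians have discretion over concomitant medication and over stopping or modifying the study product. These are the routes by which knowledge of treatment at the site could reach the results.

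The third element is timing. Two studies run side by side under what reads as one A/B scheme, one is due to finish first, and the Blinding section refers only to the completion of a single study.

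**Working it through.** The plan states no figure for predictability, so there is none to reproduce. The inputs are 1:1 allocation and a block of 6 (Randomization), consecutive numbers and two letters (Allocation Concealment), and 72 children per stratum (Power Calculation, reading its similar sample size as 72 in each). I assume that enrolling staff see each letter used and can count position within the stratum's list.

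**Letters known with certainty.** A block has 3 A and 3 B, giving 20 equally likely orders. Once one letter is used up, the rest are forced, so the number forced equals the length of the final run.
- Final run of 1: 2 × C(4,2) = 12 orders
- Final run of 2: 2 × C(3,1) = 6 orders
- Final run of 3: 2 × C(2,0) = 2 orders
- Mean = (12×1 + 6×2 + 2×3)/20 = 30/20 = 1.5 per block, and 1.5/6 = 25%

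**Letters guessed correctly.** The best guess is the letter used less so far. In every block 3 draws move back towards balance, and all 3 are guessed correctly. Draws made at a tie are right half the time. All other draws are wrong.
- Ties can occur before draws 1, 3 and 5. Their probabilities are 1, C(2,1)×C(4,2)/20 = 12/20 = 0.6, and again 0.6, which sum to 2.2.
- Expected correct = 3 + 2.2/2 = 4.1 per block, and 4.1/6 = 68.3%, against 50% by chance

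**Per stratum.** 72/6 = 12 blocks. That gives 12 × 1.5 = 18 letters certain in advance and 12 × 4.1 = 49.2 correct guesses.

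**With a unique kit number per child.** Past labels carry no information, so guessing returns to 50%, and one code break exposes one child.

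**Overlap of the two studies.**
- Nonvaccinated: June 2018 + 3 months = about September 2018 for submission
- Vaccinated: January 2017 + 2 years = about January 2019
- Difference: about 4 months

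This places the opening of the key at the end of the 3-month window; opening it sooner would lengthen the overlap. The article gives no accrual rate. If vaccinated recruitment were even over 24 months, 4/24 of 72 is about 12 children.

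**The case against.** The strongest answer is that 25% and 68% describe letters, not treatments. Knowing that the next bottle is B does not say whether B is active. The bottles are identical, and the contents look and taste alike. That stands. A reader might infer that staff can predict treatment for a quarter of the children, and the documents do not support this. Staff would also need to know or believe which letter is active, and to keep a tally by stratum. A mistaken belief could still steer enrolment, but a guess does not unmask anyone.

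A reader might also infer that publishing the nonvaccinated report will unblind the vaccinated study, or make it in effect open-label. The documents do not support that either. They do not say that the letters mean the same in both strata, or that the key will be opened to the team still enrolling. The Study Design section describes one registered trial, so blinding until completion can be read as barring early opening. Even on the worst reading, children enrolled and assessed before the key is opened stay blinded.

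Other points stand in part. A person without clinical involvement prepares the list, lists are already separate by stratum, and the envelopes are sound. Each caregiver sees only one child's bottle, so block predictability does not reach the diary directly. A fixed block of 6 is not in itself an error, and details of code custody may sit in the full protocol. None of this removes the weakness of combining two visible letters with a published block length, both of which the article itself fixes.

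**Conclusion.** The point holds as a design weakness that should be fixed, not as a demonstrated failure of blinding. Given staff who see past letters and count within stratum, the next letter is certain for 25% of children and guessable for 68%. The effect on enrolment depends on knowledge of, or a belief about, which letter is active.

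That unmasking one child unmasks all children under the same code follows directly from using two letters. The risk to the vaccinated study is conditional on two things the text leaves open: shared letters, and a key opened for the first report to people still enrolling or assessing. If both hold, vaccinated children enrolled over roughly 4 months could be unblinded. The ambiguity in the Blinding section is real, because the article treats the work both as one trial and as two studies.

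**What to change.** 1. **Allocation Concealment.** For children not yet enrolled, replace A and B with a unique kit number tied to each randomization number and assigned away from the site. This removes the information in past labels and confines any code break to one child.
2. **Randomization.** Generate the remaining lists with randomly varied block sizes that are not disclosed to the site or published. Non-disclosure matters: by the same enumeration, a block of 4 whose size is known is more predictable than a block of 6 (33% certain, 71% guessable).
3. **Blinding.** State one of two rules. Either the code stays closed to site staff and outcome assessors until both strata are complete, or each stratum has its own independent code, with the vaccinated key sealed until that study's database is locked. The first rule also protects children already enrolled under A/B, but the team could not see a nonvaccinated report that identifies the arms until vaccinated recruitment ends. The second lets the first report go ahead on time, but only for children not under a shared code.

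The cost is relabelling the remaining bottles with the manufacturer, regenerating the remaining list while recruitment is under way, and recording the change with the Ethics Committee and the registry. Product, dose, sample size and analysis do not change. The clarification of the Blinding section costs only a sentence and can be made whether or not relabelling is feasible.

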### Blinding

The study products (active and placebo) will be packaged in identical bottles. Contents will look and taste the same. Researchers, caregivers, outcome assessors, and a person responsible for the statistical analysis will be blinded to the intervention until the completion of the study. The information on intervention assignments will be stored in a sealed envelope in a safe place in the administrative part of the department. The personal information about potential and enrolled participants will be stored in a locker within the study site, accessible to the involved researchers only.

### Compliance

The caregivers will be asked to bring the remaining study product and diary to the study site at the end of the intervention period. Compliance with the study protocol will be checked by measuring the volume left unused. Based on previously published trials, it seems appropriate to consider those participants receiving <75% of the recommended doses as noncompliant.

### Power Calculation

The primary outcome of the study is the duration of diarrhea. Based on available data in the literature, the average duration of gastroenteritis in children is 5 to 7 days [3]. We assume that a clinically significant difference in the effectiveness of *L reuteri* DSM 17938 versus placebo will shorten the duration of symptoms by 24 hours (±24 hours). To detect such a difference in the duration of diarrhea between the study groups with a power of 90% and alpha of 0.01, a sample of 60 children is needed. Assuming approximately 20% loss to follow-up, we aim to recruit a total of 72 children for this study. A similar sample size for rotavirus vaccinated and nonvaccinated children is planned. Sample size calculations were performed with StatsDirect version 2.3.8 (StatsDirect Ltd).

At the Department of Paediatrics of St Hedwig of Silesia Hospital, there are 300 admissions of children with diarrhea per year and the same number of such patients who present to the emergency room. Assuming that 20% of these children will be eligible for the study, we will achieve adequate participant enrollment to reach the target sample size during 1 year of recruiting for rotavirus nonvaccinated children. Recruitment of rotavirus-vaccinated children may be slower (up to 2 years). In Poland, rotavirus vaccination has been recommended since 2006; however, vaccine reimbursement is not available. Hence, currently, the rotavirus vaccination coverage rate is low (12.7% [23] to 30% [24]), likely due to the high vaccine cost.

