## Methods

### Study Design

This study is designed as a randomized, double-blinded, placebo-controlled trial with 1:1 allocation, and it is described in more detail in the subsequent sections. The trial was registered at ClinicalTrials.gov [NCT02989350], and any important changes in the protocol will be implemented there.

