### Statistical Analysis

All analysis will be conducted on an intention-to-treat basis, including all patients in the groups to which they are randomized for whom outcomes are available (including drop-outs and withdrawals). Descriptive statistics will be used to summarize baseline characteristics. The Student *t* test will be used to compare mean values of continuous variables for approximating a normal distribution. For nonnormally distributed variables, the Mann-Whitney U test will be used. The chi-square or Fisher exact test will be used, when appropriate, to compare percentages. For continuous outcomes, differences in means or differences in medians (depending on the distribution of the data), and for dichotomous outcomes, the RR and number needed to treat, all with a 95% CI, will be calculated. The difference between study groups will be considered significant when the *P* value is <.05, when the 95% CI for RR does not include 1.0, or when the 95% CI for MD does not include 0. All statistical tests will be 2-tailed and performed at the 5% level of significance. Two independent reports (rotavirus-vaccinated and nonvaccinated children) are planned.

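### The sample size is derived at alpha 0.01, but the primary outcome will be tested at two-sided 5%, so the stated 90% power does not describe the planned test

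*Protocol article*

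**What the plan says.** Under Power Calculation, the protocol article names the outcome used for sizing: "The primary outcome of the study is the duration of diarrhea". The assumed effect is that treatment "will shorten the duration of symptoms by 24 hours (±24 hours"). The requirement follows: "with a power of 90% and alpha of 0.01, a sample of 60 children is needed". The recruitment target is then set: "Assuming approximately 20% loss to follow-up, we aim to recruit a total of 72 children for this study". Allocation is equal; Study Design describes a "randomized, double-blinded, placebo-controlled trial with 1:1 allocation".

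Under Statistical Analysis, the decision rule uses a different level: "The difference between study groups will be considered significant when the *P* value is <.05", or "when the 95% CI for RR does not include 1.0, or when the 95% CI for MD does not include 0". The section also states: "All statistical tests will be 2-tailed and performed at the 5% level of significance". It makes no exception for the primary outcome.

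Nowhere does the article explain the 0.01. It is not described as an adjustment for the two planned reports or for the reviews by the safety board, and it is not described as a deliberate margin.

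**The concern.** A sample size statement is meant to give the operating characteristics of the primary test. Here the alpha in that statement differs from the alpha of the only test described, so the quoted 90% power belongs to an analysis that the article does not plan to run.

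The practical difficulty is a primary result with P between .01 and .05. It is a positive result under Statistical Analysis, but it misses the level at which the trial was sized. If the two sections are not reconciled before unblinding, a reader of the report cannot be sure that the level was settled independently of the data.

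**Working it through.** **Inputs**

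- Difference: 24 h (Power Calculation).
- Standard deviation: 24 h. The article writes only ±24 hours; reading this as the SD is an assumption, supported by the reproduction below.
- Power 90%, alpha 0.01 (Power Calculation).
- Two-sided 5% (Statistical Analysis).
- 1:1 allocation (Study Design).

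**Reproducing the 60**

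Normal approximation for two means: n per arm = 2 × (z₁₋α/₂ + z₁₋β)² × (SD/difference)².

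At two-sided 0.01: 2 × (2.576 + 1.282)² × (24/24)² = 29.8, so 30 per arm and 60 in total. This matches the article exactly.

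| Alpha | Sides | n per arm | Total |
|---|---|---|---|
| 0.01 | two | 30 | 60 |
| 0.01 | one | 27 | 54 |
| 0.05 | two | 22 | 44 |
| 0.05 | one | 18 | 36 |

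Only two-sided 0.01 gives 60. The 0.01 is therefore the value used in the calculation and not a misprint for 0.05.

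**Power of the planned test with 60 evaluable children**

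The standard error of the difference is 24 × √(2/30) = 6.20 h, so the standardized effect is 24/6.20 = 3.87.

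- Two-sided 5%, normal approximation: Φ(3.87 − 1.96) = 97.2%. Noncentral t: 96.8%.
- Two-sided 1%, normal approximation: Φ(3.87 − 2.576) = 90.3%. Noncentral t: 88.2%.

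**Number needed for 90% power at two-sided 5%**

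- Normal approximation: 2 × (1.960 + 1.282)² = 21.0, rounded up by exact calculation to 22 per arm, 44 in total.
- t test: 22 per arm gives 89.97%, just short, so 23 per arm, 46 in total.

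**Where the two levels part**

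With 30 per arm and SD 24 h, a t test reaches two-sided 5% at an observed difference of about 12.4 h and two-sided 1% at about 16.5 h. An observed difference between these values meets one level and not the other.

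**Sensitivity**

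- If 20% of 72 children are lost, 72 × 0.8 = 57.6, about 58, remain. With 29 per arm, the t test has 96.3% power at 5% and 86.8% at 1%. The conclusion does not change.
- With 30 per arm at two-sided 5%, t-test power is about 89% at SD 28.5 h (close to the 28.47 h that the Introduction reports for the control group of the 2014 inpatient trial) and about 72% at SD 36 h (a value assumed for illustration).

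**The case against.** The strongest reply is that Power Calculation says only which alpha went into the sample size. It does not say that the primary outcome will be tested at 0.01. Statistical Analysis holds the only decision rule, it is explicit, and it controls each test at 5%. Sizing at a stricter level than the one used for testing is conservative for power. All of this stands, and it limits the point: the primary test is valid and prespecified, and the defect is a sample size statement that does not describe it.

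Four stronger readings are tempting, and the document does not support them.

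- **The trial is underpowered.** The mismatch works the other way: on the stated assumptions, power rises from 90% to about 97%.
- **The false-positive rate is five times the intended one.** The ratio 0.05/0.01 is arithmetically right, but 0.01 is never adopted as a level for inference, so there is no promised 1% error rate to breach.
- **Two reports push the chance of a false-positive primary to 9.75%.** The sum 1 − 0.95² = 0.0975 is correct, but it comes from planning separate reports for vaccinated and nonvaccinated children, not from this mismatch. The article does not say that success in either one is a single claim, or that 0.01 was chosen to allow for two.
- **The list of alternatives joined by "or" offers several routes to significance.** A simulated inflation to about 6% to 6.7% requires pairing a Mann-Whitney P value with a mean-difference interval on lognormal data with assumed spread. Statistical Analysis ties the relative risk to dichotomous outcomes, and the choice between means and medians to the distribution of the data. The natural reading is one 5% criterion expressed for different kinds of outcome.

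**Conclusion.** The point holds as an inconsistency between two sections. The 60 evaluable children come from two-sided alpha 0.01 and 90% power, whereas the primary outcome will be tested at two-sided 5%. For that test, 60 evaluable children give about 97% power, 7 percentage points above the stated figure, and 44 to 46 would give 90%. The consequence is a misdescribed design and an avoidable ambiguity for a primary P value between .01 and .05. It is neither a loss of power nor an invalid test.

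The figures assume a 24 h difference, ±24 h as the common SD, 30 evaluable children per arm in each report, and a comparison of means. If duration proves nonnormal and the Mann-Whitney test is used, the exact power will differ. The contradiction between the two alphas does not depend on any of these assumptions.

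**What to change.** State one two-sided alpha for the primary outcome in both Power Calculation and Statistical Analysis, before unblinding. Either route resolves the point.

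1. **Keep 5%.** This is the smallest change, because the decision rule already says so. Restate Power Calculation as about 97% power at two-sided 5% with 60 evaluable children (96.8% by t test), and say that the ±24 h is the SD. The sample size need not be cut to 44 or 46; the surplus protects against an SD larger than 24 h.
2. **Adopt 0.01, if that was the intention.** Change Statistical Analysis to P<.01 with a 99% interval for the primary outcome, leave the other outcomes at 5%, and give the power as about 88% (t test) to 90% (normal approximation). This replaces an explicit rule, so the reason for 0.01 should be stated.

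The cost is one or two sentences and no extra patients. The second route also sets a stricter bar for a positive primary result.

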**Methods:**

This will be a double-blind, placebo-controlled, randomized trial. Children between 1 and 60 months of age with AGE, defined as a change in stool consistency to loose or liquid form (according to the Bristol Stool Form scale or Amsterdam Stool Form scale) and/or an increase in the frequency of evacuations (typically ≥3 in 24 h) lasting for no longer than 5 days, will be recruited. A total of 72 children will receive either *L reuteri* DSM 17938 at a dose of 2×10^8^colony-forming units twice daily or matching placebo for 5 consecutive days. A similar sample size for rotavirus vaccinated and nonvaccinated children is planned. The primary outcome measure is the duration of diarrhea. Two separate studies and reports for rotavirus vaccinated and nonvaccinated children are planned.

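### The recruitment target of 72 does not cover the stated 20% loss: keeping 60 evaluable children needs 75, and 72 leaves about 57 or 58

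*Protocol article*

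**What the plan says.** The Power Calculation section of the protocol article names the endpoint ("The primary outcome of the study is the duration of diarrhea") and assumes that treatment "will shorten the duration of symptoms by 24 hours (±24 hours"). It states that, "with a power of 90% and alpha of 0.01, a sample of 60 children is needed". The next sentence gives the recruitment target: "Assuming approximately 20% loss to follow-up, we aim to recruit a total of 72 children for this study". The abstract repeats that target ("A total of 72 children will receive either"), and no other section gives a larger one.

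Three other statements bear on the check:

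- Statistical Analysis, on the test: "All statistical tests will be 2-tailed and performed at the 5% level of significance".
- Statistical Analysis, on who is analysed: "including all patients in the groups to which they are randomized for whom outcomes are available".
- Randomization: the list is prepared "with an allocation ratio of 1:1 and a block of 6".

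**The concern.** The allowance for loss appears to have been added as 20% of the number needed. Loss to follow-up is a fraction of the number recruited, so the number needed should be divided by the fraction retained. Adding 20% to 60 gives a target that falls back below 60 once 20% are lost.

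At stake is the accuracy of the planning statement. A reader will take it that 72 recruited children protect 90% power at alpha 0.01 against a 20% loss. The section's own figures do not support that. Because the analysis uses children with available outcomes, children lost without an outcome reduce the number analysed.

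**Working it through.** **Inputs.** All but the second come directly from the protocol article.

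- Difference: 24 h (Power Calculation).
- SD: 24 h. This reads the ±24 hours in Power Calculation as the SD, which is an inference. It is supported by step 1, where it reproduces the stated 60.
- Alpha 0.01 and power 90% (Power Calculation), two-sided (Statistical Analysis).
- Allocation 1:1 in blocks of 6 (Randomization).
- Loss: 20% (Power Calculation).

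**Step 1: reproduce the 60.** By the normal approximation,

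n per arm = 2 (z₀.₉₉₅ + z₀.₉₀)² (SD/difference)² = 2 (2.576 + 1.282)² (24/24)² ≈ 29.8, rounded up to 30.

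The total is 60, exactly as stated. So 60 is the evaluable number before any allowance for loss.

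**Step 2: reproduce the 72.**

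- Multiplying: 60 × (1 + 0.20) = 72, which matches the stated target exactly.
- Dividing: 60/(1 − 0.20) = 75, which does not match.

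**Step 3: what 72 delivers.**

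- Remaining after 20% loss: 72 × 0.80 = 57.6, that is 57 or 58 children, 2 to 3 below 60.
- Largest loss that still leaves 60: 1 − 60/72 = 16.7%.
- Shortfall in the target: 75 − 72 = 3 children.

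**Step 4: power** (difference/SD = 1, two-sided). The normal-approximation power is Φ(√(n/2) − 2.576) with n per arm. For example, 29 per arm gives Φ(3.808 − 2.576) = Φ(1.232) = 89.1%. The t-test columns use the noncentral t distribution.

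| Evaluable children | Normal, alpha 0.01 | t test, alpha 0.01 | t test, alpha 0.05 |
|---|---|---|---|
| 60 | 90.3% | 88.2% | 96.8% |
| 58 | 89.1% | 86.8% | 96.3% |
| 57 | 88.5% | 86.1% | 96.0% |

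**Step 5: separate the two sources of the gap.**

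- The inflation step alone costs 1.2 to 1.8 points by the normal approximation (90.3% to 89.1% or 88.5%).
- On the t-test basis it costs 1.4 to 2.1 points (88.2% to 86.8% or 86.1%).
- The rest of the distance from 90% to 86.8% comes from planning with the normal approximation. The t test needs 31.5 per arm, so 32 per arm or 64 in total (90.6% power), and 60 is already slightly short.

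**The case against.** The strongest reply is that the shortfall does no harm at the level at which the trial will be tested. The Statistical Analysis section sets that level at 5%, and there 57 or 58 children still give about 96% power under the same assumptions. This is correct and limits the practical weight of the point. It does not rescue the statement in Power Calculation, which is made at alpha 0.01. The disagreement between 0.01 and 5% is a separate matter and does not repair the inflation.

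Other replies stand in part:

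- **The loss is only approximate.** The protocol does qualify its 20%, and 16.7% is not far away. But 72 is exactly 60 × 1.20. The document does not show the derivation, so how 72 arose is inferred. That 72 does not cover 20% is not inferred.
- **The t-test comparison is an extra.** Planning with the normal approximation is a common convention, and the protocol switches to the Mann-Whitney test for nonnormal data. The fall from 90% to 86.8% should therefore not be charged wholly to the recruitment target. Even so, the normal approximation alone gives less than 90% after 20% loss.
- **Not every withdrawal is lost to the analysis.** Dropouts whose outcome is available are still included. Only children lost without an outcome reduce the number, but that is the loss a follow-up allowance is meant to cover.

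**Conclusion.** The point holds. With the section's own inputs, a 20% loss from 72 leaves 57 or 58 evaluable children against the 60 it requires, and the stated 90% power at alpha 0.01 is missed on either method: 88.5% to 89.1% by the normal approximation and 86.1% to 86.8% for the t test. The size is modest: 3 children in the target and about 1 to 2 points of power from the inflation step. It is a wrong figure that should be corrected, not a threat to the trial's ability to detect the assumed effect at the 5% level.

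The conclusion on numbers needs only the stated 60, 20% and 72. The power figures also assume an SD of 24 h, equal arms (28.5 per arm on average for 57) and loss that leaves no outcome. If 72 is the target for each vaccination cohort, which is how the planned similar sizes and two separate reports read, the shortfall of 3 applies to each. The text does not say this outright.

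**What to change.** Replace the sentence on loss in Power Calculation with one that the figures support. Either of these suffices without changing recruitment:

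- state that recruiting 72 allows for a loss of 16.7%; or
- state that with 20% loss about 58 evaluable children remain, giving about 87% power for the t test at two-sided alpha 0.01.

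If 60 evaluable children are to be secured under 20% loss, raise the target to 75. Because 75 is not a multiple of 6, 78 (13 blocks) fills whole blocks, and the abstract must change to match. If 90% power is wanted for the t test itself at alpha 0.01, the same arithmetic gives 64/0.80 = 80.

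The wording change costs one sentence and makes a stated figure slightly less favourable. The larger target is optional and costs 3 to 6 more children (75 or 78), in each cohort if 72 is a per-cohort figure.
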